**Fig 1 pone.0265137.g001:**
[figure not shown]
SPIRIT schedule of enrolment and assessments. AEs: Adverse Events, GAD-7: Generalised Anxiety Disorder 7-item Scale, ISI: Insomnia Severity Index Scale, MSQ: Migraine Specific Quality of Life Questionnaire, PHQ-9: Patient Health Questionnaire-9, T_0_: Timepoint 0, T_1_: Timepoint 1, T_2_: Timepoint 2, T_3_: Timepoint 3.

#### Estimated number of patients

This study aims to explore the information related to migraine management based on a registry of the patient cohort from GPHCM available in a specific time range, sample size calculation is not required since there are no pre-determined hypotheses to be tested [49]. This study adopts the consecutive sampling method for recruitment, which is recommended to reduce selection bias in non-randomised studies [49]. The estimated number of participants is approximately 400, based on the average annually outpatient visit numbers at the headache clinic of GPHCM between July 2018 and July 2020.

#### Exposures and confounders

In this real-world observational study, CHM treatment is defined as the main exposure. Participants being treated with CHM solely and those treated with a combination of conventional prophylactic treatment and CHM will be considered as two subcohorts for analyses.

Measured confounders in this study include comorbidities of migraine (depression, anxiety and insomnia, evaluated by PHQ-9, GAD-7, and ISI, respectively), gender, baseline severity of migraine (duration, average frequency, average pain NRS and analgesics consumption at entrance), association with the menstrual cycle (pure menstrual migraine vs menstrually related migraine vs non-menstrual migraine), and aura (migraine with aura vs migraine without aura).

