## Objectives

This observational study aims to 1) evaluate the effects and safety of individualised CHM for adult migraine in a real-world setting; 2) identify factors that contribute to clinical outcomes of CHM for migraine; 3) summarise the common patterns of CHM for migraine and its comorbidities; and 4) report on the characteristics of migraine patients who seek CHM management, including their preferences and concerns associated with CHM therapies for their migraine.

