#### Interventions

Participants will receive individually tailored treatment determined by their headache specialist in the GPHCM; these include CHM in the form of herbal decoction, granules or patented pill, alone or in combination with western medicine or other treatment procedures such as acupuncture. The treatment plan will be based on discussion between individual participants and their headache specialist, with no limitations or interference set by this study.

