#### Data collection

The study will employ a structured CRF (S1 File), which has been specifically designed for this study, including demographic information, symptoms, treatment details, relevant validated questionnaires, participants’ feedback and adverse events (AEs). Face-to-face data collection will be conducted at baseline, while evaluations at other timepoints can be completed using online CRFs or hard copy CRFs, according to participants’ preference. Online data collection will be conducted via the online survey service provider Wenjuan.com (www.wenjuan.com). Participants will be required to take migraine diary and record details of each migraine attack (S2 File). Data of patient-reported MBS, treatments, examinations and diagnostic information will also be extracted from the clinical records by the researcher.

The data to be collected from CRF is outlined below:

*Demographic and general information*. Demographic information including age, gender, general information such as family history, migraine subtypes and other medical histories will be collected upon participant enrolment.

*Patients’ preferences and concerns*. Patients’ preference and concerns regarding CHM treatment for migraine will be collected upon participants’ enrolment.

*Migraine frequency*. Defined as the number of migraine attacks in four weeks. An attack that is interrupted or rescued by sleep or medications but relapses within 48 hours will be considered as one migraine attack; attacks that are separated by an entire 24-hour period will be considered as two distinct attacks [40]. A 50% reduction in migraine frequency within a evaluation interval will be defined as response.

*Migraine days*. Defined as the number of days with migraine headache within each evaluation interval (four weeks) [41].

*Migraine duration*. Defined as the average duration of each migraine attack.

*Pain intensity*. Evaluated via numeric rating scale (NRS), which is an 11-points scale with 0 indicating no pain and 10 indicating the most severe pain. This outcome will provide data regarding the maximal pain intensity prior to taking abortive medication, as well as the average pain intensity across each observational intervals.

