*Analgesic consumption*. Data collected under this category include the type, amount and frequency of acute medication, participants’ behaviour when purchasing and using analgesics. The quantity of medications will be standardised using medication quantification scales [42], where available.

*Migraine-Specific Quality of Life Questionnaire version 2*.*1 (MSQ)*. A 14-item patient-reporting outcome instrument that measures the impact of migraine on a patient’s health-related quality of life. The domains cover role function-restrictive, role function-preventive and emotional function [43].

*Generalised Anxiety Disorder 7-item (GAD-7) Scale*. An efficient, practical, patient-reporting scale, which is commonly used for rapid screening and evaluating the presence and severity of anxiety disorder, especially in outpatient settings [44].

*Patient Health Questionnaire-9 (PHQ-9)*. A self-administrative scale to screen, diagnose, monitor and measure the severity of depression [45].

*Insomnia Severity Index (ISI)*. A brief self-reporting instrument measuring the patients’ perception of both nocturnal and diurnal symptoms of insomnia [46, 47].

*Satisfaction of treatment*. Evaluated using 5-point Likert scale [48] at each observational timepoint.

*AEs*. Participants will be asked to report any AEs possibly related to prescribed treatments, analgesics or concomitant medications, such as diarrhea, dental ulcer, insomnia in CRFs at observational visits.

During data collection, the researcher will report patients’ scores of GAD-7, PHQ-9 and relevant AEs to the corresponding clinicians to assist in clinical management.

Migraine diary is a tool for patients to record information of migraine attacks and monitor the frequency, duration, severity, associated symptoms and medication consumption of migraine attacks over time. Data collected from migraine diary will be cross-checked with CRFs as a supplementary method to ensure data accuracy.

Clinical records are referred to collect the following information:

*Treatments*, *examinations and diagnoses*. Treatment prescriptions and courses, results of laboratory and medical imaging examinations, Chinese medicine syndrome diagnosis, and western medical diagnoses will be obtained from clinical records.

*Patient-reported MBS*. Any other symptoms such as dry mouth, constipation, abdominal distention, which have been reported by participants, will be extracted from clinical records.

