#### Analytical methods

Data analysis will be conducted in relation to the study objectives:

To summarise participants’ demographic characteristics, preferences and concerns, descriptive analyses will be conducted. Such descriptive analyses will be conducted in subcohorts of patients with various levels of predefined exposures, and compared analysis will be conducted, if appropriate. Categorical variables, including gender and satisfaction degree, will be presented using frequencies and percentages; quantitative variables such as disease duration and migraine frequency will be described with mean values and standard deviation.To display the utilisation pattern of CHM for migraine and to summarise patient-reported MBS, cluster analyses and machine learning algorithms such as Apriori Algorithm [50] will be performed. Apriori Algorithm is a common method to identify core herb pairs and herb combinations [51–53]. Multiple correlation analysis and multivariable regression analysis will be conducted to explore factors related to clinical outcomes, where possible.To evaluate the effects of CHM for adult migraine, generalised estimated equation will be adopted to compare longitudinal differences of clinical outcomes. Disease risk score and instrumental variables will be introduced to control measured and unmeasured confounders, respectively. Missing data will be handled using R-MICE package for the quantitative outcome measures at each evaluation timepoint.

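### CHM is the declared main exposure, but both defined subcohorts receive it, so the planned GEE yields a before-after change and an add-on contrast, not the effect of CHM

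*Protocol article*

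**What the plan says.** Objective 1 (Protocol article, Objectives) is to "evaluate the effects and safety of individualised CHM for adult migraine in a real-world setting". The Abstract, under Methods and analysis, likewise says that GEE will be used to evaluate effects of CHM.

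Exposures and confounders fixes the exposure: "In this real-world observational study, CHM treatment is defined as the main exposure". It then fixes the groups: "Participants being treated with CHM solely and those treated with a combination of conventional prophylactic treatment and CHM will be considered as two subcohorts". No group without CHM is defined there.

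Interventions lists the treatments as follows: "these include CHM in the form of herbal decoction, granules or patented pill, alone or in combination with western medicine", or with other procedures such as acupuncture.

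Analytical methods links the objective to the model: "To evaluate the effects of CHM for adult migraine, generalised estimated equation will be adopted to compare longitudinal differences of clinical outcomes". It adds a disease risk score for measured confounders and instrumental variables for unmeasured ones. The limitations paragraph of the Discussion concedes that there is no run-in and no randomisation, and mentions recall bias and confounders. It offers the same two methods against confounding. It does not mention that a comparator without CHM is missing.

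**The concern.** An exposure effect needs people, or person-time, at different levels of that exposure. The article names the exposure and the groups, and the groups do not differ in it. What differs between them is conventional prophylaxis.

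That leaves the change from T0 to T3 as the only quantity that could be read as an effect of CHM. Patients enter at their first visit to this hospital for migraine, when attacks may be worse than usual, and they may receive western medicine or acupuncture as well. A fall after entry therefore mixes any CHM effect with regression to the mean, natural course and co-treatment.

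At stake is the first objective. An estimate that an inert treatment could also produce would stand in the results as the effect of CHM, with a disease risk score and instruments suggesting that confounding had been dealt with.

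**Working it through.** The article gives no effect size, variance, attack rate or power figure, so there is no stated number to reproduce. The check has two parts.

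**1. What the GEE can estimate from the defined subcohorts**

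Inputs: four assessments (T0 to T3, every four weeks over 12 weeks, Study design) and two subcohorts, both on CHM (Exposures and confounders). Write a model with six columns: intercept, CHM, prophylaxis, post-baseline, CHM × post, prophylaxis × post.

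- In both subcohorts CHM = 1, so the CHM column equals the intercept, and CHM × post equals post.
- Six columns minus two duplicates leaves rank 4. A numerical check with 400 patients and four visits also gives rank 4.
- The estimable time terms are *post* (the before-after change in patients on CHM alone) and *prophylaxis × post* (how that change differs when conventional prophylaxis is added).
- No coefficient for CHM is estimable.

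This only formalises the definitions: CHM = 1 for everyone is how the two subcohorts are defined, not an independent result. A disease risk score adjusts a comparison of exposed with unexposed patients, and an instrument works by shifting exposure. With CHM constant, neither has anything to act on for CHM. Both can be used for the prophylaxis contrast.

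**2. How large a before-after change could be with no treatment effect**

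Assumptions, none of them in the article: each person has a true mean μ, gamma distributed with mean m and SD s; the count in each four-week period is Poisson(μ); treatment does nothing; response is a 50% reduction from baseline. Two settings are used: m = 3, s = 2 and m = 4, s = 2.5. The entry rule is varied, because the result depends on it.

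*Strong selection* (chance of entry proportional to recent attacks). Expected baseline is E[μ²]/E[μ] + 1 and expected follow-up is E[μ²]/E[μ], with E[μ²] = m² + s².
- m = 3, s = 2: (9 + 4)/3 = 4.33, so 5.33 falls to 4.33 (−1/5.33 = −19%).
- m = 4, s = 2.5: (16 + 6.25)/4 = 5.56, so 6.56 falls to 5.56 (−1/6.56 = −15%).

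The fall of one attack is an identity of this entry rule, whatever m and s are.

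*Weak selection* (at least one baseline attack). With θ = s²/m and k = m²/s², P(no attack) = (1 + θ)^−k, and the fall is [m(1 + θ)^−(k+1)] / [1 − (1 + θ)^−k].
- m = 3, s = 2: θ = 1.333, k = 2.25, P = 0.149; fall = (3 × 0.149/2.333)/0.851 = 0.22 attack.
- m = 4, s = 2.5: θ = 1.5625, k = 2.56, P = 0.090; fall = (4 × 0.090/2.5625)/0.910 = 0.15 attack.

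Simulation with 2,000,000 patients per setting agrees:

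| Entry rule | Change (m = 3, s = 2) | Responders | Change (m = 4, s = 2.5) | Responders |
|---|---|---|---|---|
| At least one attack | −0.22 | 31% | −0.16 | 26% |
| Proportional to square root of attacks | −0.60 | 32% | −0.57 | 26% |
| Proportional to attacks | −1.00 | 32% | −1.00 | 26% |

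The mean fall depends heavily on the entry rule. The responder share hardly moves, so it mainly reflects month-to-month variation rather than selection at entry.

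**The case against.** The strongest reply is that CHM exposure may well vary. Eligibility does not require CHM. Study design records courses and dosage and keeps collecting data after treatment is discontinued. Analytical methods mentions various levels of predefined exposure. A disease risk score and instruments themselves presuppose variation, and the exact GEE contrast could sit in a fuller plan. Part of this stands: one cannot say that no CHM contrast could ever be formed from these data. But the mention of exposure levels concerns the descriptive and comparative summaries of participants, and the only levels the article predefines are the two CHM-containing ones. This is not missing detail: exposure, groups, model and claim are all stated, and they do not fit together.

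A second reply is that the study tests no predetermined hypotheses and asks for caution in interpretation. That excuses the absence of a sample size calculation. It does not turn a before-after change into an effect of CHM, and the admitted limitations do not include the missing comparator.

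A third reply, that the illustration rests on assumptions, is right. It shows a possible order of size, not a prediction.

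A reader might also infer that the measurement method inflates the change, since "Face-to-face data collection will be conducted at baseline, while evaluations at other timepoints can be completed using online CRFs or hard copy CRFs" and "Data collected from migraine diary will be cross-checked with CRFs as a supplementary method to ensure data accuracy". The article does not support a direction. Later visits may use either form, the diary is a supplementary check whose effect on the values is not stated, and recall at baseline could undercount attacks as easily as overcount them.

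**Conclusion.** The point holds as a mismatch between the stated exposure, the defined groups and the stated conclusion. As written, the GEE gives an uncontrolled 12-week change under CHM-containing care and a confounded contrast for adding conventional prophylaxis. Neither is the effect of CHM in Objective 1 and the Abstract, and the planned confounding methods cannot supply it.

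Under the stated assumptions and zero treatment effect, the spurious fall is about 0.15 to 1 attack per four weeks, depending on how strongly recent attacks drive care-seeking, and about 26 to 32% of patients would count as responders. The structural conclusion does not depend on these figures.

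Three stronger readings are not supported. The GEE is not useless: it can validly describe within-patient change. A fall of a full attack is not to be expected in general, because it follows from one entry rule. The safety part of Objective 1 is not affected in the same way.

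**What to change.** - In the Abstract, Objectives and Analytical methods, restate the GEE time contrast as *12-week change under CHM-containing care*.
- Label the subcohort contrast *adding conventional prophylaxis to CHM*, and state that the disease risk score and instrumental variables apply to this contrast.
- Because eligibility does not require CHM, report registered patients whose T0 plan contains no CHM as a separate comparison cohort if numbers allow. Label it *CHM-containing versus non-CHM care* and state that it is confounded by indication. It should not be called the effect of CHM: these patients may be on other treatments, and the group may be very small.
- Add the missing CHM-free comparator to the limitations in the Discussion.

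The cost is wording, plus one optional analysis group drawn from patients already registered. Data collection does not change. The downside is a more modest claim for the first objective.

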Migraine is usually managed with medications for relieving symptoms in the acute stage, and with prophylactic treatment for reducing the frequency and severity of future attacks. The acute medications include aspirin, nonsteroidal anti-inflammatory drugs, paracetamol, antiemetics, steroids, and triptans. Prophylactic pharmacotherapies include calcium channel blockers, beta-blockers, tricyclic antidepressants, candesartan, pizotifen, angiotensin-converting enzyme inhibitors, selective serotonin reuptake inhibitors (SSRI), serotonin norepinephrine reuptake inhibitors (SNRI), antiepileptics, Botulinum toxin A and calcitonin gene-related peptide (CGRP) [14, 15]. Among them, only tricyclic antidepressants, SSNI and SNRI can be adopted for migraine comorbid with depression [14–16]; Botulinum toxin A is suggested for chronic migraine. Medical devices for migraine include occipital nerve block, vagus nerve stimulation, transcutaneous supraorbital nerve stimulation and transcranial magnetic stimulation [14–16]. However, approximately 30–40% of migraineurs are dissatisfied with current treatments, especially those suffering from chronic migraine [17, 18] and migraine with comorbidities [19–23], citing insufficient treatment effects, low tolerability, and unbearable side effects [24].

Acknowledging the above-mentioned limitations, there is an urgent need to identify alternative or complementary therapies to assist current conventional managements. Chinese herbal medicine (CHM), which is often prescribed to migraine patients in China [25], has gained clinical research evidence as an effective alternative or complementary therapy for migraine in recent years. However, most of the existing evidence has been generated from randomised controlled trials (RCTs) [26–30] and RCT-based systematic reviews [31–34]. Under controlled settings, RCTs usually apply strict selection criteria and provide unified treatments to all participants [35]. Such design may not reflect the complexity of migraine and its comorbidities [36], nor reflect the real-world practice of CHM which is commonly tailored according to individual’s syndrome differentiation [37]. Hence, the research evidence obtained from previous explanatory RCTs and systematic reviews need to be supplemented with more real-world evidence.

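### The two treatment subcohorts leave no clear place for CHM plus acupuncture or another procedure without conventional prophylaxis, and procedures are not among the listed confounders

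*Protocol article*

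**What the plan says.** The Interventions section of the protocol article describes care agreed between patient and specialist, "with no limitations or interference set by this study". CHM may be given "alone or in combination with western medicine or other treatment procedures such as acupuncture".

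Exposures and confounders then sets out the analysis groups. First, "CHM treatment is defined as the main exposure". Second, "Participants being treated with CHM solely and those treated with a combination of conventional prophylactic treatment and CHM will be considered as two subcohorts for" the planned analyses. The article does not define *solely*. The measured confounders listed there are depression, anxiety and insomnia scores, gender, baseline severity (including analgesic consumption at entry), relation to the menstrual cycle, and aura. Neither acupuncture nor any other procedure is on the list.

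Analytical methods takes these groups over: "Such descriptive analyses will be conducted in subcohorts of patients with various levels of predefined exposures", with comparisons where appropriate. The generalised estimating equation for the effects of CHM is not restricted to the subcohorts. A disease risk score and instrumental variables are planned for measured and unmeasured confounders respectively.

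Acute medication is handled on its own track. The Introduction separates it from prevention ("Migraine is usually managed with medications for relieving symptoms in the acute stage, and with prophylactic treatment"). Data collection makes analgesic consumption an outcome ("Data collected under this category include the type, amount and frequency of acute medication"). Data collection also says that treatment prescriptions and courses will be taken from the clinical records.

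**The concern.** The Interventions section sets CHM alone against CHM with acupuncture, so by the article's own usage a patient receiving both is not on CHM alone. Nor is that patient on conventional prophylaxis: the Introduction lists drugs under that heading and names medical devices separately, and acupuncture appears in neither list. A pattern of care that the protocol names therefore has no clear place in the groups it fixes for analysis.

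The CHM-only subcohort is the nearest the study comes to showing outcomes under CHM without another preventive treatment. If patients with procedures are in it, its results mix CHM with an active co-treatment. If they are not, they drop out of the subcohort descriptions and comparisons. If the choice between the two is left until outcome data are in hand, it can also be influenced by them.

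**Working it through.** The article gives no figure to reproduce on this point. The check is a cross-tabulation of permitted care against the two subcohorts, followed by an illustration of size.

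**Step 1. Patterns of care.** All patients considered here receive CHM. Interventions allows three additions, each present or absent: a conventional prophylactic (P), acute western medicine (A), and acupuncture or another procedure (X). That gives 2 × 2 × 2 = 8 patterns. The four with P fall in the combination subcohort, provided other additions are ignored. The four without P depend on what *solely* means.

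**Step 2. The four patterns without P, under each possible meaning of *solely*.**

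| Pattern | (a) nothing but CHM | (b) acute medication allowed, procedures not | (c) no conventional prophylactic |
|---|---|---|---|
| CHM only | placed | placed | placed |
| CHM + A | in neither group | placed | placed |
| CHM + X | in neither group | in neither group | counted as CHM only |
| CHM + A + X | in neither group | in neither group | counted as CHM only |
| Patterns placed | 1 of 4 | 2 of 4 | 4 of 4 |

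Both patterns that contain a procedure are unplaced under (a) and (b) and carry the CHM-only label under (c). No reading places them correctly. CHM with acute medication is unplaced only under (a).

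**Step 3. Whether later text repairs it.** The list of measured confounders contains no procedure, so a disease risk score built on that list would not include one. Analytical methods reuses the predefined exposures without adding a category. The clinical records will hold the treatments given, so the data needed to classify these patients will exist.

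**Step 4. Size, by illustration only.** Under reading (c), let a share *s* of the CHM-only group also have a procedure that adds a reduction of *d* attacks per four weeks to a reduction *c* under CHM. The group mean is (1 − s)c + s(c + d) = c + sd, so the overstatement is *s × d*. The article gives neither *s* nor *d*, so the values below are assumptions.

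| | s = 10% | s = 20% | s = 30% |
|---|---|---|---|
| d = 0.5 | 0.05 | 0.10 | 0.15 |
| d = 1.0 | 0.10 | 0.20 | 0.30 |

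For the comparison between subcohorts, the same algebra gives (s₁ − s₂)d, where s₁ and s₂ are the shares with a procedure in the CHM-only and combination groups. The distortion there can go either way, and it vanishes if the shares are equal.

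**The case against.** The strongest objection is that Interventions describes permitted care and Exposures and confounders names two analysis groups. Such lists can differ without conflict, and the exact meaning of *solely* is a detail that an article may leave to the full protocol or analysis plan. The first part stands: a reader might infer that the two sections contradict each other, but Interventions defines no analysis groups, so this is an incomplete exposure definition. The second part does not dispose of the point. The article does not leave the groups and confounders for later; it states both, and followed as written they leave a named co-treatment unplaced or unadjusted.

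A reader might also infer that patients who take acute analgesics fit neither subcohort, so that membership would depend on an outcome. The article does not support this. The subcohorts are divided by *prophylactic* treatment, and analgesic use is tracked separately as an outcome and as a baseline severity measure. The natural reading is that rescue use does not change a patient's group. Only reading (a) says otherwise, and the text does not require it.

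Nor are patients with procedures lost to the study. The subcohorts are not called exhaustive, CHM is the exposure for the whole cohort, and the treatment data are extracted for everyone. At most these patients are missing from the subcohort analyses.

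Finally, the article never says that the change within the CHM-only group will be reported as the effect of CHM by itself, and its Discussion urges caution about confounders. That limits how far the consequence can be pressed. It does not remove the co-treatment from a group labelled as CHM only, or from whole-cohort estimates presented as effects of CHM.

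**Conclusion.** The point holds for one pattern of care: CHM plus acupuncture or another procedure, without conventional prophylaxis. On every reading of *solely* these patients are either outside both subcohorts or labelled as CHM only, and no listed confounder accounts for the procedure. They stay in the whole-cohort analysis, where the procedure is likewise unadjusted.

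The number of patients and the size of any bias cannot be computed, because the article reports no co-treatment frequencies or effects. The range of 0.05 to 0.30 attacks per four weeks rests on assumed shares of 10% to 30%, assumed added effects of 0.5 to 1.0 attacks, and a common response to CHM in patients with and without a procedure. The gap in the classification depends on none of these. It is worth closing before the analysis, but it does not invalidate the study.

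**What to change.** In Exposures and confounders, classify patients by two flags taken from the clinical records: conventional prophylactic (yes/no) and acupuncture or other procedure (yes/no). Keep the CHM-only label for patients with neither. Then either report patients with a procedure as a separate category, or include the procedure flag in the between-group and whole-cohort models. A covariate does not clean an unadjusted within-group change, so the restriction on the label is needed in either case.

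Add one sentence saying that acute analgesic use, being an outcome and a baseline severity measure, does not determine group membership. This only settles a term that the article leaves undefined.

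The change affects classification and modelling only, and no patient's treatment. It needs a few lines of text and one extra variable from records that will be extracted anyway. The downside is smaller groups, including a smaller CHM-only group, within an expected total of about 400. Using the flag as a model term limits the splitting if few patients have procedures.
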